**Figure 1 F1:**
[figure not shown]
Study design.

The fecal sample analysis will apply metagenomics, and the feces and blood samples will be analyzed using an untargeted metabolomics method. We intend to explore the stratification of gut microbial communities in patients who underwent cardiac surgery with CPB and to analyze the variation in metabolites in patients' plasma and fecal samples. Predictive biomarkers and possible pathogenesis of FUO and hemodynamic instability after CPB will also be provided by clinical outcome analysis combined with a multi-omics study.

### Study Population

The inclusion criteria are the following. Patients between 18 and 85 years of age who will undergo extracorporeal circulation during cardiac surgery, will be admitted to the ICU and provide written informed consent. The control group will be 30 healthy persons aged between 18 and 85 without digestive disease. The exclusion criteria are as follows; patients would be excluded if they (1) had a fever before surgery, regardless of the etiological evidence of infection; (2) had anti-infective treatment before surgery; (3) had gastrointestinal surgery that left the digestive system dysfunctional; (4) had a history of CPB in the last 6 months; or (5) rejected or abandoned ICU therapeutic intervention. The control group will be excluded if they are taking certain medications.

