#### Sample Collection

There will be 60 patients enrolled as the case group and 30 healthy people as the control. After fasting for at least 6 h but not more than 10 h, venous blood will be collected by direct venepuncture or established venous access from patients enrolled. Plasma will be taken from the blood and remain in Eppendorf tubes at −80°C for 1 h. Fresh fecal samples will be obtained (sometimes aided by glycerinum) and stored at −80°C before analysis. In the control group, samples will be collected once. In the case group, feces and blood samples will be acquired at the following time points (Figure 1): (1) T1: 1 day before cardiac operation; and (2) T2: within 24–72 h of ICU admission, sampling must be performed before patients start oral feeding.

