#### Grouping by Outcomes

The primary outcome is patients with cardiovascular surgery with CPB and healthy people.

The secondary outcomes are as follows.

After sample collection, the case group will be selected and divided into two groups according to their clinical outcomes.

Sepsis group (sub grouped by suspected or documented infection) and non-sepsis group;Survivors and non-survivors based on the 28-days survival.

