The current view suggests that intestinal bacteria may lead to sepsis in several ways. First, intestinal bacteria and bacterial products are transferred to distant organs through blood flow. However, this view lacks bacteraemic evidence. Second, intestinal bacterial metabolic products are transferred to distant organs through the lymphatic pipeline. Third, in critically ill patients, changes in the intestinal flora and metabolites can cause systemic inflammatory reactions and the body's immune response, leading to sepsis (26). We suspect that intestinal dysbacteriosis after CPB is a possible mechanism of inflammation and anti-inflammatory immune imbalance, and that bacterial translocation leads to infection and sepsis. In the critical care unit, most common clinical interventions [e.g., enteral feeding (28), proton-pump inhibitors (29), systemic catecholamines (28), and systemic antibiotics (30)] will change intestinal bacteria. It was recently shown that exposure to broader-spectrum antibiotics during hospitalization is associated with dose-dependent increases in the risk of subsequent sepsis (31). Moreover, in critically ill patients, a significant decrease in bacterial diversity was observed. In more than 30% of patients, a single bacterial genus makes up >50% of the gut microbiota (32). Furthermore, in many cases of prolonged critical illness, only two-member pathogen communities remain. The communities contain bacteria associated with the genera Enterococcus and Staphylococcus, and the family Enterobacteriaceae comprises the majority of these communities (33).

Several studies have shown that the role of inflammation in heart failure may promote the gut microbiota as a cardio-metabolic target for intervention (34). The gut microbiota can secrete large amounts of amyloids and lipopolysaccharides, which might produce some proinflammatory cytokines, such as tumor necrosis factor (TNF) (35). TNF could reduce mitochondrial activity, alter calcium homeostasis, and impair β-adrenergic signaling in cardiomyocytes to act as a suppressor of cardiac function (36). It can be seen that the study of intestinal microecology is of great significance for the postoperative inflammation response or sepsis and cardiac function. Therefore, we are reasonably confident that intestinal flora research can be an important breakthrough in the study of the pathogenesis of postoperative sepsis. Differences in species of the intestinal flora also affect the prognosis of sepsis.

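### Any digestive disease bars a healthy control, but only dysfunction after gastrointestinal surgery bars a patient, so the primary patient-versus-healthy contrast is partly confounded by non-surgical digestive disease

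*Protocol article*

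**What the plan says.** Study Population sets separate eligibility rules for the two arms.

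- Controls, digestive disease: "The control group will be 30 healthy persons aged between 18 and 85 without digestive disease". Study Design repeats the requirement, and the Abstract expresses it as absence of intestinal illness.
- Controls, drugs: "The control group will be excluded if they are taking certain medications". No drug is named.
- Patients, digestive disease: the only such exclusion is "had gastrointestinal surgery that left the digestive system dysfunctional".
- Patients, drugs: the only such exclusion is "had anti-infective treatment before surgery".

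Grouping by Outcomes makes this comparison the primary one: "The primary outcome is patients with cardiovascular surgery with CPB and healthy people". Sample Collection gives the sizes: "There will be 60 patients enrolled as the case group and 30 healthy people as the control". Controls are sampled once. Patients are sampled at T1, the day before the operation, and at T2, 24 to 72 hours after ICU admission. The Multi-Omic Data Analysis Plan compares cases with controls by a linear mixed-effect model at a two-sided 0.05 level and names no term for digestive disease in that comparison.

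**The concern.** The two arms of the primary contrast are selected by different rules on a characteristic that bears directly on what is measured. A patient with, say, inflammatory bowel disease or chronic diarrhoea and no relevant surgery is eligible. The same condition would exclude a control. Part of any patient-versus-healthy difference in flora or metabolites, including one seen at T1 before any surgery, could then reflect digestive disease that the design removed from one side only.

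Healthy controls will inevitably differ from cardiac patients in heart disease; that comes with the design. The difference in the digestive criterion does not, and it can be avoided. Collecting more subjects would not reduce it.

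**Working it through.** **Criteria side by side**

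| Factor | Healthy control | Surgical patient |
|---|---|---|
| Non-surgical digestive disease | Excluded | Eligible |
| Dysfunction after gastrointestinal surgery | Excluded, if it counts as digestive disease | Excluded |
| Preoperative anti-infectives | Unknown (list not named) | Excluded |
| Other drugs | Unknown (list not named) | Eligible |

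Only the first row is an asymmetry that the text itself establishes. The last row depends on a list that is not shown.

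**Illustration of size**

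The protocol states no prevalence, effect size, SD or power, so there is no figure of its own to reproduce. What follows shows scale only.

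Inputs from the document: 60 cases, 30 controls, two-sided 0.05. Assumed inputs: a share p of cases with digestive disease, and a shift d (in SD units, same direction in all affected patients) in a given feature. Normal approximation for two means at one time point:

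- SE = √(1/30 + 1/60) = √0.05 = 0.224 SD.
- Difference detectable with 80% power = (1.960 + 0.842) × 0.2236 = 0.63 SD.
- Bias b = p × d.
- Chance of a significant result when the true adjusted difference is zero = Φ(b/SE − 1.96) + Φ(−b/SE − 1.96).

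| p | d | Bias (SD) | False-positive chance per feature |
|---|---|---|---|
| 10% | 0.5 | 0.05 | 5.6% |
| 10% | 1.0 | 0.10 | 7.3% |
| 20% | 0.5 | 0.10 | 7.3% |
| 20% | 1.0 | 0.20 | 14.5% |
| 30% | 1.0 | 0.30 | 26.9% |
| 50% | 1.0 | 0.50 | 60.9% |

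At p = 10% to 20%, 60 × 0.10 = 6 to 60 × 0.20 = 12 patients would carry the factor, against 0 of 30 controls. The last two rows show how the bias grows if the share is larger. If different digestive diseases shift a feature in opposite directions, the net bias is smaller than shown.

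**What restriction costs in precision**

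Dropping 6 to 12 cases leaves 54 to 48.

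- 54 cases: SE = √(1/30 + 1/54) = 0.228; detectable difference 2.802 × 0.228 = 0.64 SD.
- 48 cases: SE = √(1/30 + 1/48) = 0.233; detectable difference 2.802 × 0.233 = 0.65 SD.

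The loss is 0.01 to 0.03 SD on a starting value of 0.63 SD.

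**The case against.** **The within-patient comparison already answers the surgical question.** Each patient has T1 and T2 samples, and stable digestive disease largely cancels between them. Sepsis versus non-sepsis is compared among patients admitted under identical rules. This stands, and it limits the damage: those contrasts are not touched by the asymmetry. It does not rescue the comparison that the protocol calls primary, because both T1 and T2 against controls remain exposed.

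**The protocol does not claim that the whole difference is due to surgery.** A reader might infer that the primary contrast attributes digestive disease and drug effects to heart surgery. No section says so. The supportable statement is narrower: the contrast is partly confounded.

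**Flora-altering drugs.** A reader might also infer that such drugs exclude controls but not patients. The document does not support this. Patients treated with anti-infectives before surgery are excluded. The controls' drugs are unnamed, and a condensed article may well leave that list to the full protocol. The Discussion's remark that "proton-pump inhibitors (29), systemic catecholamines (28), and systemic antibiotics (30)] will change intestinal bacteria" concerns interventions in the critical care unit, so it does not show that patients arrive on such drugs.

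**A factor that is zero in controls by design cannot be adjusted for.** This tempting argument is wrong. The factor varies among cases. With a group term and an indicator for digestive disease at one time point, the group coefficient is the mean of unaffected patients minus the mean of controls, which is the same estimate that restriction gives.

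**Unnamed adjustment may be in a plan that is not shown.** True, and the absence of a covariate list is not the point here. The point is the two stated eligibility rules, which differ.

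**Conclusion.** The concern holds for digestive disease. Controls are screened for any such disease and patients only for dysfunction left by gastrointestinal surgery, so the primary patient-versus-healthy contrast is partly confounded by non-surgical digestive disease. The true size cannot be derived from the document. On an assumed 10% to 20% prevalence and a 0.5 to 1.0 SD shift, the bias is 0.05 to 0.20 SD, well below the roughly 0.63 SD detectable with 80% power, but enough to raise the per-feature false-positive chance to between 5.6% and 14.5%.

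For drugs other than anti-infectives the concern is only conditional. It applies if the controls' list includes drugs that patients may take.

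**What to change.** 1. Using the past medical history that Observation and Data Recording already lists, run the case-control comparison in patients without digestive disease, or include a digestive-disease indicator in the mixed model. State in advance which of the two is the main analysis.
2. Apply the controls' digestive criterion to the remaining patients where feasible. At 31 January 2020, 45 of 60 cases had been collected, so this reaches at most 15. Late cases would then be selected differently from early ones, which is why step 1 is needed in any event.
3. Read the perioperative change from T1 versus T2 within patients, not from patients versus healthy controls, and say so. Even with equal criteria, the remaining patient-versus-healthy difference includes heart disease.
4. For drugs, name the controls' list. If it goes beyond anti-infectives and patients' preoperative use is recorded, repeat the comparison in patients not taking those drugs. Otherwise state this as a limitation; preoperative drugs other than antibiotics are not among the recorded items that the article names.

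The cost is one restricted analysis on data already collected, a short amendment to Study Population, possibly slightly slower recruitment of the last cases, and a small loss of cases from this comparison. How far past medical history captures digestive disease depends on how completely it was taken.

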### Study Protocol

#### Recruitment

Patients in the department of cardiac surgery who underwent cardiac surgery with cardiopulmonary bypass will be assessed for eligibility for the study according to the inclusion and exclusion criteria. Additionally, the control group will be recruited from people who will have health checks at Peking Union Medical College Hospital or the healthy volunteers. When people agree to participate, the informed consent forms will be signed in duplicate. Recruitment will be terminated when the case group reaches 60 cases. The study protocol was approved by the Ethics Committee. The committee will oversee the study to monitor data safety. The collection started on August 1, 2018 and is expected to finish on September 30, 2020. We have collected a total of 67 samples, including 45 cases of cardiac surgery patients in the case group and 22 healthy people in the control group have been collected on January 31, 2020.

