### Multi-Omic Data Analysis Plan

The data will be analyzed according to the case and control groups, sepsis and non-sepsis groups, and survivor and non-survivor groups, or some other classifications based on the pathophysiology.

Metagenomic and metabolomics statistical analysis will be performed using commercial software. To account for dependencies in repeatedly measured observations within a subject, a linear mixed-effect model will be used to assess the differences between the case group and the control group. Statistical analysis will be performed using SPSS (version 22, SPSS, Chicago, IL). A two-sided significance level of 0.05 will be used for statistical inferences. Combining principal component analysis (PCA), partial least squares discriminant analysis (PLS-DA), and orthogonal partial least square discriminant analysis (OPLS-DA), different metabolite profiles will be identified.

Receiver operating characteristic (ROC) analysis will be conducted to evaluate the utility of the potential biomarkers selected. Multivariate logistic regression analysis will be used to show the correlation between each factor and prognosis and changes in intestinal flora. A *p* < 0.05 will be considered statistically significant.

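### No matching of the healthy controls on age or sex is stated, and no role for age or sex in the patient-control analysis, although the protocol calls that contrast primary

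*Protocol article*

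**What the plan says.** **Who the controls are.** Under Study Population: "The control group will be 30 healthy persons aged between 18 and 85 without digestive disease". The only other control-specific criterion there is "The control group will be excluded if they are taking certain medications", with the drugs not named. Under Recruitment, "the control group will be recruited from people who will have health checks at Peking Union Medical College Hospital or the healthy volunteers". Neither section, nor Study Design, states an age band, a sex quota or a matching rule.

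**Who the cases are.** Study Population admits "Patients between 18 and 85 years of age who will undergo extracorporeal circulation during cardiac surgery", so the age limits are the same in both groups. Patients have a drug exclusion of their own: anti-infective treatment before surgery.

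**Numbers.** Sample Collection: "There will be 60 patients enrolled as the case group and 30 healthy people as the control". By 31 January 2020, Recruitment reports "45 cases of cardiac surgery patients in the case group and 22 healthy people in the control group".

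**Rank of the contrast.** Grouping by Outcomes: "The primary outcome is patients with cardiovascular surgery with CPB and healthy people".

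**Analysis.** The Multi-Omic Data Analysis Plan says that "a linear mixed-effect model will be used to assess the differences between the case group and the control group". The reason given is within-subject dependence, and no covariate is named. Metabolomics Analysis selects metabolites by t or Wilcoxon tests together with PCA and PLS-DA. The one multivariable regression, a logistic model, concerns prognosis and flora changes. It lists no factors and is not tied to the patient-control contrast. Observation and Data Recording collects age and sex but gives them no analytic role.

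**The concern.** Identical eligibility limits of 18 to 85 fix only the extremes. They allow a young group of volunteers or health-check attendees to be set against an older surgical group, or a different sex mix, and nothing stated prevents it. If a microbial or metabolite feature varies with age or sex, an unadjusted comparison attributes that variation to being a patient.

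At stake is the list of features reported as distinguishing patients from healthy people. The plan also uses the selected features as candidate biomarkers in ROC analysis, so a feature that only tracks age could be carried forward.

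The choice of controls is a design matter that a later analysis plan cannot undo. Once the controls are collected, only adjustment is left.

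**Working it through.** The article gives no power calculation, effect size or age distribution, so there is no stated figure to reproduce. The check has two parts.

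**1. Does anything stated remove an age or sex imbalance?**

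- Eligibility: the same range in both groups, which is not balance.
- Recruitment source: health checks or volunteers, with no quota.
- Mixed model: handles repeated samples within a person. A subject-level random effect does not remove a difference in age between groups.
- t/Wilcoxon tests: two-group comparisons with no covariates.
- Logistic regression: aimed at a different question.

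Nothing stated does so.

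**2. How large could the effect be? (scenario)**

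Inputs from the protocol article: 60 cases, 30 controls, two-sided 0.05.

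Assumed inputs, not in the documents: age SD 12 years within each group; correlation r between feature and age of 0.2 or 0.3; mean age gap of 10 or 20 years; no true group effect; one value per person.

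- Spurious standardised difference: d = r × gap / 12.
- Standard error: √(1/30 + 1/60) = 0.2236.
- Noncentrality: d / 0.2236, with 60 + 30 − 2 = 88 degrees of freedom.
- False-positive rate: two-sided rejection probability of the noncentral t.

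| Gap | r | d | Noncentrality | False-positive rate |
|---|---|---|---|---|
| 10 years | 0.2 | 0.17 | 0.745 | 11.4% |
| 10 years | 0.3 | 0.25 | 1.118 | 19.8% |
| 20 years | 0.2 | 0.33 | 1.491 | 31.4% |
| 20 years | 0.3 | 0.50 | 2.236 | 59.9% |

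Weaker correlation gives much less. With the gap D in SD units and r = 0.1, a normal approximation gives 5.6% at D = 0.5, 7.3% at D = 1 and 10.3% at D = 1.5.

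A simulation of 4,000 runs per setting compared the unadjusted and the age-adjusted linear model under no group effect:

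| D | r | Unadjusted | Age-adjusted |
|---|---|---|---|
| 0.5 | 0.2 | 7.0% | 4.8% |
| 1 | 0.2 | 14.2% | 4.3% |
| 1 | 0.3 | 26.1% | 5.5% |
| 1.5 | 0.3 | 50.8% | 5.1% |

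Adjustment brings the error back to about 5%.

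**Price of adjustment.** The variance of the group effect is multiplied by 1 + (60/90)(30/90)D² = 1 + (2/9)D². That is 1.06 at D = 0.5, 1.22 at D = 1 and 1.50 at D = 1.5.

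**What the last controls can do.** 30 − 22 = 8 controls were outstanding. If the first 22 averaged 20 years younger than the cases and the last 8 had the cases' mean age, the gap would fall only to (22/30) × 20 = 14.7 years. Steered recruitment helps but cannot replace adjustment.

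**The case against.** **Covariates may be specified elsewhere.** A reader might infer that the case-control analysis is planned as unadjusted. The article does not say that. It is silent on the mixed model's covariates, and a fuller protocol or analysis plan, not shown, could list them. This objection stands, and the point is limited to what is stated. It does not reach the absence of stated matching, which concerns recruitment already under way.

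**Medication.** A reader might also infer that controls face a drug exclusion and patients none. That is not so: patients with pre-operative anti-infective treatment are excluded. Since the controls' list is unspecified, the overlap is unknown and nothing is built on it here.

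**Other contrasts are unaffected.** Each patient is sampled the day before surgery (T1) and again within 24-72 h of ICU admission (T2). The T1-T2 change compares patients with themselves, and sepsis versus non-sepsis uses no healthy controls. This stands and narrows the harm, but the article still gives first rank to patients versus healthy people.

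**The figures are assumptions.** This also stands. In an untargeted panel many features may be only weakly related to age, and for those the inflation is small.

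**Conclusion.** The concern holds in this form: no matching on age or sex is stated, and no role for age or sex is stated in the analysis of the contrast called primary. The plan as written allows an age or sex difference to be read as an effect of case status.

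Confidence is high on the missing matching and low on the size of any bias, since its direction and magnitude are unknown. The rates of 11-20% (10-year gap) and 31-60% (20-year gap) apply only to features correlated with age at 0.2 to 0.3, with an assumed age SD of 12 years. They are not a forecast for the whole panel.

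Two stronger conclusions would go too far. The documents do not show that the controls are younger than the patients. Nor would balancing age and sex isolate an effect of CPB: heart disease, comorbidity and medication differ between patients and healthy people by design.

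**What to change.** 1. Include age and sex as fixed effects in the case-control mixed model. If a fuller plan already does this, one sentence in the protocol settles it.
2. Use the same adjusted model, in place of the t/Wilcoxon tests, for the case-control metabolite comparison. Otherwise that route remains unadjusted.
3. Confirm that age and sex are recorded for controls. The recording section is written around patients and does not say so explicitly, although the eligibility range requires a control's age to be known.
4. Recruit the controls still outstanding (8 of 30 at 31 January 2020) into the age-sex strata where controls are short relative to cases.
5. Use the within-patient T1-T2 change for the effect of surgery with CPB. State that heart disease, comorbidity and medication stay inseparable from case status in the patient-control contrast.

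**Cost.** Two covariates, a recruitment instruction and slightly slower control recruitment. Adjustment loses some precision if ages differ: group-effect variance rises about 1.06-fold at a gap of 0.5 SD and 1.22-fold at 1 SD.

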## Method and Analysis

### Study Design

This protocol is designed as a prospective observational case–control study in patients who underwent cardiopulmonary bypass (CPB) due to cardiac surgery. Thirty healthy persons aged between 18 and 85, without digestive system disease, will be selected as the control group. The case group will include patients admitted to the intensive care unit (ICU) after cardiac surgery with CPB, which is performed by the Department of Cardiac Surgery of Peking Union Medical College Hospital. The patients enrolled should be divided into two groups according to their outcomes: one group of non-sepsis patients and the other group of sepsis patients after cardiac surgery. Sample collection will be terminated when each group receives 30 cases. These 60 cases will be regarded as the case group. Additionally, all the patients we observe will be further divided into survivors and non-survivors based on 28-days survival. Feces and blood samples will be obtained at certain time points (Figure 1).

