#### Definition

The clinical criteria according to the third international consensus (Sepsis-3) (17):

Sepsis: suspected or documented infection and an acute increase of ≥2 SOFA points.

Suspected infection group will be identified as those who had body fluids sampled for culture and received antibiotics but had a negative culture result.

The documented infection group will be identified as those who had body fluids sampled for culture with a positive result.

Survivors: Patients that survive for 28 days or more after surgery.

Non-survivors: Patients that survive <28 days after surgery.

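### Exclusion (5) can remove patients after enrolment and the T1 sample, which may bias the 28-day survival comparison and, to a lesser extent, the sepsis comparison

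*Protocol article*

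**What the plan says.** The Study Population section of the protocol article lists five exclusions for the patient group. The first four are preoperative: fever, anti-infective treatment, earlier gastrointestinal surgery with lasting dysfunction, and recent CPB. The fifth applies to patients who "rejected or abandoned ICU therapeutic intervention".

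Inclusion in the same section looks forward. It takes patients "who will undergo extracorporeal circulation during cardiac surgery, will be admitted to the ICU and provide written informed consent". Under Sample Collection, the first sample is "T1: 1 day before cardiac operation" and the second is "T2: within 24–72 h of ICU admission".

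The comparison groups are formed later. Grouping by Outcomes states: "After sample collection, the case group will be selected and divided into two groups according to their clinical outcomes". Study Design sets the quota: "Sample collection will be terminated when each group receives 30 cases". It adds that "all the patients we observe will be further divided into survivors and non-survivors based on 28-days survival", and the Definition section gives "Non-survivors: Patients that survive <28 days after surgery".

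**The concern.** An eligibility criterion should rest on facts known at enrolment. Abandoning ICU treatment is an event during follow-up, and it can occur in the same days in which sepsis is diagnosed and deaths occur. If the patients who leave this way are sicker, or are dying, then removing them selects on a correlate of the outcome that defines the groups.

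At stake is mainly the survivor versus non-survivor comparison, together with the ROC and prognosis regression analyses in the Multi-Omic Data Analysis Plan that would use the same patients. The Introduction says that patients with worse outcomes are of particular interest, and those are the patients this criterion could remove. The criterion also conflicts with the Study Design statement that all observed patients are split by survival: a patient sampled at T1, observed in the ICU and then removed under (5) is not.

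**Working it through.** **1. Order of events.** Consent is given while surgery and ICU admission are still in the future. T1 follows one day before surgery, then surgery, ICU admission, T2 at 24–72 h, and 28-day status. Abandonment of ICU treatment can fall only after ICU admission, so after T1 and either before or after T2. Refusal of ICU care could also occur before surgery; that part of (5) is an ordinary eligibility fact.

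**2. What happens to a removed patient.** Sampling continues until 30 sepsis and 30 non-sepsis cases are reached, so a removed patient is replaced and the final 60 do not show the loss. The End Point section ends observation at 28 days, at death, or when the patient is ready for ICU discharge. Abandonment is not on that list. No section keeps these patients in the survival comparison.

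**3. Figures available.** The article gives no abandonment rate, no planned number of deaths and no power calculation, so there is no stated figure to reproduce. Its only mortality figure is 3% in-hospital, from a cited cohort (Introduction). Everything below rests on assumed inputs.

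**4. Number of non-survivors.** Let m be true mortality, a the share of deaths excluded and b the share of survivors excluded. Then

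observed mortality = m(1−a) / [m(1−a) + (1−m)(1−b)].

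For m = 10%, a = 30%, b = 0: 0.07 / (0.07 + 0.90) = 7.2%, or 4.3 deaths in 60 instead of 6.0. Expected deaths in 60 with b = 0:

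| m | none excluded | a = 10% | a = 30% | a = 50% |
|---|---|---|---|---|
| 3% | 1.8 | 1.6 | 1.3 | 0.9 |
| 10% | 6.0 | 5.5 | 4.3 | 3.2 |
| 20% | 12.0 | 11.0 | 8.9 | 6.7 |

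Setting b = 1% changes these by at most about 0.1 deaths. Since half of the 60 are septic by design, a mixed assumption fits the design better. With 3% mortality in the 30 non-sepsis patients and 10% or 30% in the 30 sepsis patients, expected deaths are 30 × 0.10 + 30 × 0.03 = 3.9, or 30 × 0.30 + 30 × 0.03 = 9.9. One lost non-survivor is then 1/3.9 = 26% or 1/9.9 = 10% of that group.

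**5. Effect on the group contrasts.** A simulation of 2,000,000 patients let a latent severity drive a marker (correlation 0.5), sepsis (50%), death (10.9%) and, in some scenarios, exclusion.

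| Exclusion | Patients excluded | Deaths excluded | Survival contrast (SD) | Sepsis contrast (SD) | Observed mortality |
|---|---|---|---|---|---|
| None | 0 | 0 | 0.52 | 0.41 | 10.9% |
| Random | 5.0% | 5.1% | 0.53 | 0.41 | 10.9% |
| By severity | 6.6% | 16.7% | 0.47 | 0.38 | 9.7% |
| By severity and dying | 5.5% | 39.1% | 0.35 | 0.38 | 7.0% |

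Random exclusion leaves both contrasts unchanged apart from rounding. Outcome-related exclusion reduces the survival contrast by up to about a third (0.353/0.525 = 0.67) and the sepsis contrast by about 9% (0.377/0.413 = 0.91).

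**The case against.** - **Timing.** *Rejected* may mean refusal of ICU care before surgery, which is harmless. Recruitment also speaks of assessing patients who already had surgery, so the enrolment point is loose. This stands as a limit on the point. *Abandoned* cannot be read as preoperative, though, and screening after surgery would still let (5) act on postoperative events.
- **Bias is inferred.** A reader might infer that (5) definitely biases the comparisons. The article gives no rate of abandonment, no reasons and no link to severity, so only *can bias* is supported.
- **Mortality.** A reader might infer that reported mortality will be too low. The listed outcomes are group comparisons, and mortality in a 30/30 quota sample is set partly by the quota, so the study does not target such an estimate.
- **The 3% figure.** A reader might infer from 0.03 × 60 = 1.8 that one exclusion costs half the non-survivors. That figure is in-hospital mortality in a general cardiac-surgery cohort, and it ignores the septic half of the sample. The small number of deaths is also a problem with or without (5).
- **Restricting to treated patients may be deliberate.** The aim is to observe patients under routine interventions, and deaths after care is declined may differ in cause. This has weight, but it argues for a with-and-without analysis rather than removal on a post-enrolment event.
- **Left to the full protocol or SAP.** Counts and sensitivity analyses may be there, and their absence from the article is no fault. The criterion itself, however, is fixed in the text shown.

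**Conclusion.** The point holds in a limited form. As far as (5) covers patients who abandon or refuse ICU treatment after enrolment and T1, it is a post-enrolment exclusion acting while the comparison groups are being defined, and it conflicts with the Study Design statement on splitting all observed patients by survival.

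Whether it causes bias depends on one assumption outside the document: that stopping treatment is related to severity or dying. Under that assumption the survival comparison is affected directly. The sepsis comparison is affected less, because the quotas fix the group sizes and the bias works only through which patients fill them. The direction and size in this study cannot be derived; the simulated changes show what is possible, not what to expect. The wording should be corrected, but the point does not undermine the study as a whole.

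**What to change.** The change concerns eligibility wording and analysis sets only; it alters no patient's care.

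- Restrict (5) to refusal of ICU care known before enrolment.
- Keep enrolled patients who had CPB and later decline or stop ICU treatment in the survival comparison, with T1 data, any T2 data and 28-day vital status.
- In the sepsis comparison, use their sepsis status where it was established before care stopped. Do not count truncated observation as non-sepsis by default.
- Report how many there are, including any already removed: Recruitment reports 45 cases collected by 31 January 2020, and new wording alone will not recover patients dropped before then.
- Show the comparisons with and without these patients.
- Keep consent withdrawal and failure of other eligibility criteria, such as not having CPB, as valid reasons for removal.

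The cost is a wording change, a look back through the enrolment log and a few vital-status checks. Some T2 samples will be missing, so these patients may add nothing on postoperative change. Deaths after care is declined may differ in cause from the others, which the with-and-without analysis makes visible.
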